#### Early maladaptive schemas

Early maladaptive schemas will be assessed with the self-report Young Schema Questionnaire second version (YSQ-2) [65–68]. The YSQ-2 is the most commonly used measure of early maladaptive schemas [65]. The YSQ-2 consists of 205 items, to be rated along a 6-point Likert scale, which measures the severity of 16 maladaptive schemas. The Dutch YSQ-2 has good reliability and convergent and discriminant validity [69].

#### Schema modes

Schema modes will be assessed with the Schema Mode Inventory (SMI), a 118-item, self-report questionnaire measuring 16 modes [65]. These modes can be divided into 4 types: healthy modes, parent modes, child modes and coping modes. All items are rated on a 6-point Likert scale. The Dutch SMI has an excellent test-retest reliability and the convergent and divergent validity of the subscales are satisfactory [70].

#### Schema and modes severity scores

Patients will rate the severity of their three most dominant schemas and modes on a scale from 0 (no burden at all) to 10 (a lot of burden) on a weekly basis.

### Analyses

Analyses will be conducted according to the intention-to-treat principle. Differences between the intervention and control group on the various outcome measures (BSI-53, EQ-5D-5 L, secondary outcome parameters) will be analyzed using linear mixed-models, more specifically random coefficient analysis, which accounts for missing observations [71]. In these analyses, study site and patient will be included as random effects (with observations nested in patients and patients nested in study sites) and study arm and full versus subthreshold personality disorder as fixed effects. Interactions will be tested 1) between time of observation and study arm and 2) between this interaction and full versus subthreshold personality disorder, to check whether the intervention effect is different for patients with a full or subthreshold personality disorder. All analyses will be controlled for the baseline population characteristics described above.

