### Sample size calculation

The only RCT comparing group SFT with TAU was conducted among younger adults with borderline personality disorder and found a between group Cohen’s *d* effect size (ES) of 2.0 on the Brief Symptom Inventory (BSI-53) [33]. For our power analysis, we tuned down the expected ES to 0.5 (medium effect) for two reasons. First, the ES of 2.0 was partly due to absence of an effect of TAU [34] while meta-analysis of psychotherapy in geriatric psychiatry shows an average pre-post ES of 0.4 for TAU [17]. Second, an open study on group SFT reported a pre-post Cohen’s *d* ES of 0.8 among older adults with mixed cluster B and C personality disorders [21]. Applying a 2-sided alpha of 0.05 and a power of 80% to detect an ES of 0.5, requires 63 patients per arm. Although compensation for dropout is not necessary according to the CONSORT criteria when performing intention to treat analyses (http://www.consort-statement.org/), we aim to include 140 patients in order to compensate for 10% early dropouts during the waiting-list period. Differences in the scores between the intervention and control group on the various outcome measures (BSI-53, EQ-5D-5 L, YSQ and SMI) will be analyzed using linear mixed-models accounting for missing data and relevant confounders.

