### Randomisation, blinding and treatment allocation

A stratified block randomisation will be performed aimed to assign participants evenly (1,1) over the two conditions [35]. Randomisation will be performed per study site and stratified by the presence of a full versus subthreshold cluster B/C personality disorder (PD – 1 criterion). Participants will be randomized in blocks when 8 to 16 consecutive patients have consented to participate at a specific study site. Randomisation will be performed centrally using online randomisation software QuickCalcs of GraphPad (http://www.graphapd.com/quickcalcs/randMenu).) by an independent investigator who will be blind to patient characteristics. Patients will be randomized in even patient numbers per stratum. In case of an uneven number of participants per stratum, the next even number of patients will be randomised and the last allocation will be forwarded to the next block randomisation with an uneven number of patients within that stratum. After randomisation, patients and their responsible geriatric psychiatrist or psychologist will be informed of their allocation. The therapists delivering the intervention will be informed which patients can be invited for group SFT + PMT.

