### Assessments

Data are collected at the following moments: at the screening, baseline (T1), at the end-of-treatment (T2, i.e. 6 months after baseline for the TAU group), and finally at 6- and 12-month follow-up (T3 and T4). Many outcomes consist of self-report measures. Some are assessed by structured telephone interviews conducted by research assistants who will be blind about the treatment allocation of the interviewed patient. These interviews include assessment of socio-demographic characteristics and psychiatric history (at baseline only) as well as medical consumption and costs in the past 3 months. Personal information about potential and enrolled participants will be stored confidentially. Table 1 shows the questionnaires used at each assessment.

**Table 1 Tab1:** .shows the questionnaires used at each assessment

	Time of assessment				
	Screening	Baseline	Post treatment assessment	6-month Follow-up	12-month Follow- up
Primary outcomes					
Psychological distress: BSI-53		X	X	X	X
Health-related quality of life: EQ-5D-5 L		X	X	X	X
Medical consumption & costs		X	X	X	X
Secondary outcomes					
Life satisfaction: Cantril’s Ladder		X	X	X	X
Mental wellbeing: WEMWBS		X	X	X	X
Personality functioning: SIPP-SF		X	X	X	X
Interoceptive body awareness: MAIA		X	X	X	X
Psychotropic drug use & treatment received					
Mood variability: Mood-Zoom		X	X	X	X
Characteristics					
Personality disorders: SCID-5-PD Cluster B & C	X				
Mental disorders: MINI-Plus	X				
Cognitive screening: MoCA	X				
Psychiatric treatment history: telephone interview		X			
Socio-demographics: telephone interview		X			
Chronic illnesses: LASA questionnaire		X			
Early life-events: NEMESIS questionnaire		X			
Alcohol use: AUDIT		X			
Current smoking: NEMESIS questions		X			
Physical activity: NEMESIS question		X			
Personality traits: PID-5-SF		X			

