### Primary outcome parameter

Psychological distress in the past week, as indicated by the sum score of the Brief Symptom Inventory 53 item version (BSI-53), is the primary clinical outcome parameter. The BSI-53 is a self-report questionnaire and an abbreviated version of the Symptom Checklist-90 (SCL-90) [33, 42]. The BSI is validated for older adults and preferred over the SCL-90 since validation studies in older adults did not indicate any information loss compared to the SCL-90 [43]. We have chosen for psychological distress as the primary outcome parameter since 1) older patients with personality problems are rarely referred to geriatric mental healthcare for personality problems specifically, but nearly always for associated affective symptoms and 2) the study includes patients with a variety of personality disorders. Since the reliability of the Dutch BSI-53 subscales is rated as good and their convergent and divergent validity has been found to be satisfactory [42], subscale scores will be examined as secondary outcome parameters.

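### The treatment effect is tested as a time-by-arm interaction with no primary BSI-53 contrast named, while the 80% power belongs to a single two-group comparison

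*Protocol article*

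**What the plan says.** **Model and test.** The Analyses section specifies "linear mixed-models, more specifically random coefficient analysis, which accounts for missing observations". Site and patient are random effects; study arm and full versus subthreshold disorder are fixed effects. It continues: "Interactions will be tested 1) between time of observation and study arm and 2) between this interaction and full versus subthreshold personality disorder". The second interaction is described as a check on whether the intervention effect differs by stratum, so the first, time by arm, is the intervention effect. The coding of time is not given, and neither a visit nor a contrast is singled out.

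**Visits.** Design and Assessments place measurements at baseline (T1), end of treatment (T2, about 6 months), and 6 and 12 months after that (T3 and T4, about 12 and 18 months). The intervention section puts the last group session at week 26, so treatment ends at about T2.

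**Power.** The Sample size calculation says: "Applying a 2-sided alpha of 0.05 and a power of 80% to detect an ES of 0.5, requires 63 patients per arm". The effect size is argued from pre-post changes: an open study of group SFT with 0.8, and for usual care, "meta-analysis of psychotherapy in geriatric psychiatry shows an average pre-post ES of 0.4 for TAU". No time point is stated.

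**Primary outcome.** In the Methods section on the primary outcome, the BSI-53 sum score "is the primary clinical outcome parameter". The abstract and Design also name psychological distress alone. Table 1 puts three rows under its primary heading: BSI-53, "Health-related quality of life: EQ-5D-5 L", and medical consumption and costs.

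**The concern.** A power statement should describe the test that will decide the trial. Here one section sizes a single difference between two means, and another tests an interaction over four occasions. The interaction can be a slope difference (1 df, linear time) or a joint test of three visit differences (3 df, categorical time). Neither is the comparison that was powered.

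The slope version matters most. Treatment covers roughly the first third of the 18 months. A benefit that arrives by T2 and then stays level or recedes is poorly described by a constant rate of divergence between the arms, so a real end-of-treatment benefit could be reported as no effect. With categorical time, a significant joint test does not say at which visit, or in which direction, the arms differ.

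**Working it through.** **Inputs from the protocol article:** two-sided alpha 0.05, d = 0.5, 63 per arm, 1:1 allocation, visits at about 0, 6, 12 and 18 months. **Assumed, because not given:** SD 1 at each visit (except in the random-slope case), no missing data, and within-patient correlation ρ of 0.5 to 0.7 (compound symmetry). Alternatives for the held course are AR(1) with 0.7, and a random slope variance of 0.02 to 0.04 per (6 months)².

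**1. The plan's own figure.** n per arm = 2(1.96 + 0.84)²/0.5² = 63. Check: 0.5/√(2/63) = 2.81, giving 80.1% power. Inflated for 10% dropout: 126/0.9 = 140. Both figures reproduce, for a single unadjusted contrast.

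**2. Linear time by arm.** With time in 6-month units (0, 1, 2, 3), Σ(t − 1.5)² = 5. Under compound symmetry the SE of the slope difference is √[2(1 − ρ)/(63 × 5)], which is 0.0563, 0.0504 and 0.0436 at ρ = 0.5, 0.6 and 0.7. The fitted slope is Σ(t − 1.5)d(t)/5.

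| Difference at T2, T3, T4 | Slope per 6 months | Power at ρ = 0.5 / 0.6 / 0.7 |
|---|---|---|
| 0.5, 0.5, 0.5 (held) | 0.15 | 76 / 85 / 93% |
| 0.5, 0.4, 0.3 | 0.08 | 30 / 36 / 45% |
| 0.5, 0.25, 0 | −0.025 | 7 / 8 / 9% |

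In the last row the slope points the wrong way. For the held course, AR(1) gives 68%. A random slope variance of 0.02 or 0.04 gives SE = √[2(0.5/5 + 0.02)/63] = 0.0617 or √[2(0.5/5 + 0.04)/63] = 0.0667, and so 68% or 61%. The range for a held effect is therefore 61 to 93%.

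**3. What the line says at T2.** With arm as a main effect, the line fitted to (0, 0.5, 0.5, 0.5) has intercept 0.15 and slope 0.15. The fitted arm difference at T2 is 0.15 + 0.15 = 0.30, against a true 0.5.

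**4. Categorical time, 3 df.** Under compound symmetry the noncentrality is (63/2)[Σd² − (Σd)²/4]/(1 − ρ). At ρ = 0.5:
- Held: 31.5 × 0.1875/0.5 = 11.8, power 83%.
- Fading to 0.3: 31.5 × 0.14/0.5 = 8.8, power 70%.
- Fading to zero: 31.5 × 0.1719/0.5 = 10.8, power 80%.

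**5. One named contrast, baseline-adjusted, ρ = 0.5.**
- T2: 0.5/√[2(1 − 0.25)/63] = 3.24, power 90% for all three courses.
- Average of T2 to T4: residual variance (1 + 2ρ)/3 − ρ² = 0.417 and SE = √(2 × 0.417/63) = 0.115. Mean effects of 0.5, 0.4 and 0.25 give z = 4.35, 3.48 and 2.17, so power is 99%, 94% and 59%.

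The gain at T2 over the stated 80% comes from baseline adjustment.

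**The case against.** The article condenses a fuller plan, and time coding or the exact contrast may be settled in an analysis plan that is not shown. That has force against a complaint of missing detail. It does not answer the point that the article itself states a test and a power basis that do not correspond.

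Linear time is an inference. The named random effects are site and patient, with no random slope, and the reference to time of observation could mean visits. This stands: with categorical time the shape problem largely goes.

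Several stronger readings are tempting, and the document does not support them:
- **Low power.** A held effect gives slope power on either side of 80%. The large loss needs linear time and a waning effect together.
- **An expected plateau or relapse.** No such course is predicted. The Background cites a small case series in which symptoms fell during treatment and follow-up.
- **An inflated type I error from picking the best visit.** No such selection is planned, and a joint 3-df test holds its 5%.
- **Three confirmatory tests.** Table 1 has a labelling conflict. The text names one primary clinical outcome and treats EQ-5D-5L and costs within the economic evaluation.
- **The interaction read as the effect in one stratum.** That follows only if the three-way term is kept in the primary model and the stratum is reference-coded. Neither is stated.

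**Conclusion.** The point holds as a mismatch between the stated test and the power statement, together with a primary comparison that is not fixed. For the same 0.5 SD benefit at T2, the power of a linear time-by-arm test runs from under 10% to 93%. Where it falls depends on the course after T2 and on a covariance structure, neither of which is given. A single baseline-adjusted T2 contrast has about 90% at ρ = 0.5 whatever happens later. These figures assume 63 per arm with complete data, and linear time is the ordinary meaning of the named method and not an explicit statement. If time is categorical, what remains is a 3-df test (70 to 83% across the three courses at ρ = 0.5) that is not the comparison behind the 80%. The Table 1 conflict needs no assumption, but it concerns labelling only. The change is worth making before analysis because it protects the main conclusion.

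**What to change.** 1. Model time as categorical, with baseline adjustment or a common baseline mean across arms.
2. Name one primary BSI-53 contrast. The T2 difference fits the pre-post reasoning behind the sample size best; the average over T2 to T4 is also defensible if durability is the target. Treat the other visits as secondary.
3. Restate the power for that contrast, giving the assumed correlation if baseline adjustment is used.
4. Estimate the primary contrast from a model without the three-way stratum term, and fit that term in a separate model.
5. Reconcile the primary heading in Table 1 with Design and the primary outcome section by listing EQ-5D-5L and costs as economic outcomes.

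The cost is wording in the analysis section or analysis plan and one table heading, with no new data. The downside is that visits outside the named contrast lose primary status. If T2 is chosen, the maintenance of benefit becomes a secondary question.

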## Methods

### Design

We designed a multi-center randomized controlled trial with two parallel treatment groups: 20 sessions of group SFT enriched with PMT delivered over a 6-months period, versus treatment as usual (TAU) for older adults with cluster B and/or C personality disorders in specialized mental health care. Primary outcome is general psychological distress. In addition, cost-effectiveness of the intervention from a societal perspective is evaluated. Outcome measurements will be administered pre- and post-treatment as well as at 6 and 12 months post-treatment. Six mental health care organizations in the Northern Netherlands agreed to participate, one university department of geriatric psychiatry (University Medical Center Groningen) and five affiliated mental health organizations (GGZ Friesland van Andel department, GGZ Drenthe, Lentis, Dimence and Mediant). The study has been approved by the Medical Ethics Committee of the University Medical Center Groningen on May 12th, 2017 (M17.212189) and was registered in the Dutch Trial Register on August 20th, 2017 (NTR 6621).

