### Recruitment

Mental health professionals working at the different sites can inform patients about the study when a cluster B or C personality disorder is suspected. After having received oral and written study information from their mental health professional interested potential eligible patients will get an appointment with the clinical psychologist at their clinic. During this screening session, the in- and exclusion criteria for the study are formally checked by administering amongst others the SCID-5-PD and MoCA and any remaining questions the patient has about the study are answered. For patients not meeting the in- and exclusion criteria the study ends after this screening session. Patients eligible for the study, will be given another 2 weeks to consider participation. Patients willing to participate in the study, will be asked to sign informed consent and are put on a waiting-list. Only the patients who gave written informed consent are included in the study. The data from the screening appointment, will be passed on – anonymously – for inclusion in the study database. When a minimum of 8 and maximum of 16 patients have given informed consent at a specific site, baseline measurements will be conducted, after which participants will be randomized (see flowchart) Fig. 1.

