### Group Schema-focused therapy enriched with PMT

Two individual pre-treatment sessions without PMT take place before the group sessions. These are meant to make a personal treatment plan based on administering the Young Schema Questionnaire (YSQ) and Schema Mode Inventory (SMI) (see Mediators section below) and to explain the concept of group SFT enriched with PMT in more detail. The subsequent group interventions comprise 20 sessions over a period of 26 weeks. The first 18 sessions will be provided weekly after which two follow-up sessions are given at week 22 and 26. Each treatment session consists of a 2 h group session SFT and 1 h group session PMT, with a 15-min break in between. Treatment is provided according to a detailed protocol. This protocol is highly structured and based on the Dutch protocols short cognitive schema-focused group therapy [36] and experiential techniques [37, 38]. During the initial group sessions, patients will be further educated about the schema model, specifically in relation to their own three predominant schemas and coping styles (called ‘modes’ in schema focused therapy). In the second treatment phase the patients maladaptive schemas will be triggered and patients will be taught to respond in a more adaptive manner. In this treatment phase the ‘experiential imagery rescripting’ and ‘chair interventions’ will be conducted [37, 38]. All patients receive a personal schema-focussed therapy workbook for older adults. This workbook will be extended every session with a summary of the session information and homework assignments. The patients will write a weekly summary of their therapy process and fill in a ‘severity score form’. On this form patients rate the severity of their 3 predominant schemas and maladaptive modes. Based on clinical experience with older persons, geriatric themes like loss of a role in society, loss of loved-ones, comorbid somatic diseases and sociocultural beliefs in the treatment of elderly, are integrated in the treatment protocol [39, 40]. Furthermore, the protocol has been enriched with PMT to overcome the limitations of verbal therapy. During PMT, the psychomotor therapist sets up individual and group-based physical interventions to facilitate that patients experience their schemas and modes. Continuity between the verbal and psychomotor sessions is guaranteed by participation of the psychologist in the PMT as co-therapist. This way the observations pending PMT can be further analyzed in the verbal sessions.

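### The primary mixed model has no therapy-group level, although only the SFT + PMT arm is treated in groups; if outcomes correlate within groups, its standard error is too small and the stated 80% power does not allow for this

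*Protocol article*

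**What the plan says.** **Model.** The Analyses section specifies linear mixed models in which "study site and patient will be included as random effects (with observations nested in patients and patients nested in study sites"). Study arm and full versus subthreshold disorder are fixed effects. No therapy-group or therapist term is named. The same model serves the BSI-53, the EQ-5D-5L and the secondary outcomes.

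**Sample size.** "Applying a 2-sided alpha of 0.05 and a power of 80% to detect an ES of 0.5, requires 63 patients per arm". The only allowance on top of this is for loss before treatment starts: "we aim to include 140 patients in order to compensate for 10% early dropouts during the waiting-list period". No ICC or design effect appears.

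**How the groups arise.** The Recruitment section starts a batch thus: "When a minimum of 8 and maximum of 16 patients have given informed consent at a specific site". The randomisation section is "aimed to assign participants evenly (1,1) over the two conditions". On delivery of the experimental arm, the article says: "The subsequent group interventions comprise 20 sessions over a period of 26 weeks". The therapist section treats the therapy group as a unit when it samples audiotapes per group. Under Treatment as usual, a team chooses care for each patient, and the only treatment barred is group SFT.

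**Sites.** "Six mental health care organizations in the Northern Netherlands agreed to participate".

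**The concern.** Patients in one SFT + PMT group share therapists, sessions and each other for half a year. The Discussion itself suggests that group process may accelerate therapy. Some within-group correlation of outcomes is therefore plausible, and zero is not a natural default. TAU patients are not clustered in this way, so the design is partially nested: clustered in one arm, individual in the other.

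The stated hierarchy has observations, patients and sites, but not the level that delivery of the therapy creates. If that level carries variance, the confidence interval for the primary effect is too narrow and the p-value too small. Any difference that chance gives to a few therapy groups would be read as more precise evidence about the therapy than it is. The sample size makes the same independence assumption and has no slack.

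**Working it through.** **Inputs from the protocol article.** Two-sided alpha 0.05, power 80%, standardised difference d = 0.5, n = 63 per arm (Sample size calculation); batches of 8 to 16 (Recruitment; Randomisation); 1:1 allocation; six sites (Design).

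**Inferred.** Group size m = 8/2 to 16/2 = 4 to 8. Number of SFT + PMT groups = 63/8 to 63/4, about 8 to 16, so groups outnumber sites.

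**Assumed.** ICC 0.01 to 0.10, as the document gives none. SD = 1 and one time point without baseline adjustment, as in the plan's own calculation.

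**Step 1: the plan's figure.** n = 2(1.960 + 0.842)²/0.5² = 62.8, rounded up to 63. Power at 63 = Φ(0.5/√(2/63) − 1.960) = Φ(0.846) = 80.1%. Then 126/0.9 = 140. Both stated figures reproduce, for independent patients only.

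**Step 2: why the site intercept does not help.** Randomisation is 1:1 within site, so a site effect enters both arm means equally and cancels from their difference. A therapy-group effect enters the SFT + PMT mean only and stays in the difference.

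**Step 3: variance under partial nesting.**

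Var(difference) = [1 + (m − 1)ICC]/n + 1/n

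Relative to independence, the variance ratio is V = [2 + (m − 1)ICC]/2.

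- Power of a valid test: Φ(0.5/√(2V/63) − 1.960).
- Type I error of the model without a group term: 2[1 − Φ(1.960/√V)].

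Example, m = 6 and ICC 0.05: V = 2.25/2 = 1.125. The standard error is √(2.25/63) = 0.189, and power = Φ(2.646 − 1.960) = 75.4%. Type I error = 2[1 − Φ(1.848)] = 6.5%.

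| ICC (assumed) | m | V | √V (true SE / model SE) | Power at 63 per arm | Type I error as planned |
|---|---|---|---|---|---|
| 0.01 | 4 | 1.015 | 1.007 | 79.5% | 5.2% |
| 0.01 | 8 | 1.035 | 1.017 | 78.8% | 5.4% |
| 0.05 | 4 | 1.075 | 1.037 | 77.2% | 5.9% |
| 0.05 | 6 | 1.125 | 1.061 | 75.4% | 6.5% |
| 0.05 | 8 | 1.175 | 1.084 | 73.5% | 7.1% |
| 0.10 | 4 | 1.150 | 1.072 | 74.4% | 6.8% |
| 0.10 | 6 | 1.250 | 1.118 | 70.9% | 8.0% |
| 0.10 | 8 | 1.350 | 1.162 | 67.6% | 9.2% |

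**Step 4: small-sample degrees of freedom.** The table uses the normal approximation. With V₁ = [1 + (m − 1)ICC]/n on n/m − 1 df and V₂ = 1/n on n − 1 df, the Satterthwaite df are (V₁ + V₂)² / [V₁²/(n/m − 1) + V₂²/(n − 1)]. At ICC 0.05 this gives about 44, 28 and 20 df for m = 4, 6 and 8. Noncentral-t power is then 75.4%, 72.4% and 69.2%.

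**Step 5: simulation check of type I error.** 20,000 null trials per setting, single time point, six sites with site in the model, 64 per arm (16 groups of 4 or 8 groups of 8). Rejection rates for m = 4 and m = 8 were 4.8% and 5.2% at ICC 0, 5.8% and 7.6% at ICC 0.05, and 7.1% and 9.3% at ICC 0.10. The formula's pattern holds with site adjusted for.

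**The case against.** **It all depends on a positive ICC, and none is given.** This stands as a limit on size. At ICC 0.01 the power loss is about one point and the type I error barely moves. A reader might infer that the 80% power is certainly not delivered; the document does not support that flat statement.

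**The planned analysis is more efficient than the sample-size formula.** BSI-53 is measured at baseline and three later times. If baseline adjustment cuts the variance by the factor 1 − r², the ICC 0.05 loss is offset when 1 − r² = 1/V, that is r = 0.26 to 0.39 for m = 4 to 8. Such correlations are assumptions, but not extreme ones. This part stands for power. It does nothing for the standard error, which still lacks the group component.

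**All 140 might be analysed.** At 70 per arm and ICC 0.05, power is 81.4%, 79.6% and 77.9% for m = 4, 6 and 8. The plan places the 10% loss in the waiting-list period, before randomisation, so 63 per arm is the proper basis.

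**Random coefficient analysis could include more.** The only random units named are site and patient. Even a site-by-arm slope, which is not mentioned, would capture group variance only in part where a site runs several groups.

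**The detail could sit in a fuller plan.** That would cover silence. Here the nesting is written out, and it omits the level.

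**TAU may also involve groups.** Usual care can include group, day or inpatient treatment. Treating TAU patients as unclustered is therefore a modelling assumption, although the section expects mainly case management or treatment of comorbid disorders.

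**A stronger reading on costs.** A reader might infer that the cost-effectiveness bootstrap has the same fault. The economic section does not name the resampling unit, so no error can be shown there.

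**Conclusion.** The omission is certain from the text: the random-effects structure of the primary analysis lacks the therapy-group level that the design creates in one arm. For any positive within-group correlation, the planned standard error is too small and the error favours declaring a difference. Confidence is high on this and moderate on its size.

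The size depends on the assumed ICC and the inferred group size. At ICC 0.01 it is negligible. At 0.05 the true standard error exceeds the model's by 4% to 8%, and at 0.10 by 7% to 16%; type I error near 9% needs the upper ICC and the largest groups. The 80% power claim holds only for independent patients. Whether real power falls below 80% cannot be settled from the document, since the gain from baseline and repeated measures is not quantified.

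The point deserves correction before analysis because it affects the primary interval and p-value, and the remedy is one model term.

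**What to change.** 1. **Analyses section.** Add a random effect for therapy group that acts in the SFT + PMT arm only (a partially nested model). State as an assumption that TAU patients are treated as singletons. Use Kenward-Roger or Satterthwaite degrees of freedom, since only about 8 to 16 groups are expected.
2. **Data.** Keep a therapy-group identifier in the study database. Therapists already record each patient's attendance, but the article does not say that group membership reaches the database.
3. **Sample size section.** Restate the power at 63 per arm over ICC 0.01 to 0.10 and group sizes 4 to 8, on the same degrees-of-freedom basis as the analysis. State any credit taken for baseline adjustment and the correlation assumed.

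**Cost.** A slightly wider confidence interval and a less favourable stated power. The analysis change needs no extra patients. Restoring 80% by numbers alone at ICC 0.05 is a separate decision: n = (1.960 + 0.842)²[2 + (m − 1)ICC]/0.5² gives 68, 71 and 74 per arm for m = 4, 6 and 8 under the normal approximation, before any gain from baseline adjustment.
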